### Data collection and management

Personal information (including date of birth, sex, diagnosis, symptom onset and diagnosis, occupational and educational background, as well as relationship between participant dyads) will be collected from consenting participants and will remain confidential. Participants will be given a unique number that will be used on all paperwork, assessment score sheets, video and data files and all subsequent analysis documents and publications. Lists of participant names and their unique numbers (required to conduct the remote randomisation procedure) will be kept by the chief investigator at University College London (UCL) and the RA or designated local collaborator in a locked cabinet at each NHS site. Each list will only contain the names of participants based at the relevant site.

Participants will consent to be video recorded during conversations for the purposes of outcome measurement and fidelity rating and to provide clips for video feedback during intervention sessions. Semi-structured interviews will also be video recorded. All transcripts of conversation data will be anonymised using pseudonyms for named people and places. One aspect of this research study involves the detailed analysis of video recordings where faces will be fully visible. It is not appropriate to blank out faces as people’s expressions form a significant part of human communication: the focus of the intervention being piloted. If participants consent to use of recordings at conferences or in teaching, their faces will be blurred using video software. Additionally, participants (people with dementia and their CPs) will be contacted at the end of the study to re-visit consent for use of specific video clips for this purpose. No semi-structured interviews with participants or healthcare professionals will be used for the purposes of teaching or at conferences. Only the research team members will have access to the entire video-recorded dataset.

It is common practice for SLTs to ask patients to video themselves. Many patients now have their devices and will often do this. We have followed this common practice. Transfer of patient data from NHS sites to the university will be managed electronically via the secure Data Safe Haven system where site technology supports this. Where this is not possible, the chief investigator or RA will collect data from outcome assessors and local collaborators and upload it to the secure Data Safe Haven system.

The study is compliant with General Data Protection Regulations. If information disclosed by any participant leads the first author to believe that any person is at risk of harm, confidentiality will be breached to ensure safety. Given this is an NHS-embedded pilot study, delivered by local SLT collaborators, no additional data monitoring committee has been established beyond the sponsor and the BCPPA steering group. The BCPPA steering group is comprised of a PPI representative, two senior SLTs and a clinical psychologist, a professor of neurology and an associate professor in speech and language therapy. This group is independent from the sponsor and funder and meets four times annually to discuss recruitment, retention and data management.

All electronically held data including video recordings will be stored for 10 years on the UCL Data Safe Haven. This is in accordance with current University College London Records Management Policy; research findings will need to be stored by UCL as sponsor for 10 years after the research has finished. Depending on which consent option has been chosen by the participants with dementia or their consultee, and their CPs, all video data collected during the trial will also be archived on the CAVA repository. This procedure is standard practice in the Department of Language & Cognition, UCL, for video data collected from people with communication disorders including aphasia, dementia and Parkinson’s for research purposes, and has been approved by NHS ethics committees in the past for research led by the chief investigator.

### Analysis plan

Qualitative and quantitative analysis will be used for this single masked, randomised controlled pilot study. Descriptive statistics will be used to report recruitment, attendance, attrition and reasons for dropout. A CONSORT^59^ and SPIRIT ^60^ flow chart will be used to present overall recruitment to and progression through the study (figure 1). Recorded intervention sessions will be transcribed, and descriptive statistics will be used to analyse dosage. Data collated from potential and actual participants, including date of onset, will also be examined to explore patterns related to optimal dosage and schedule of the intervention. Recruitment and retention rates will be used to support sample size calculations to inform a future full trial and plan the required number of sites to meet this target. Adverse events will also be recorded, and participant interviews examined to inform future recruitment procedures.

All outcome data will be explored to test for assumptions of normalcy. If assumptions are not met, appropriate non-parametric tests will be used. Repeated-measures analyses of variance will be used with group (immediate vs deferred) as a between-subject factor and time (pre-therapy and post-therapy) as a within-subject factor. Results will be used to determine a suitable and sensitive outcome measure and perform a power calculation to determine the sample size for a fully powered trial. Conversation data will be analysed following a procedure developed for the BCA intervention^29^ to identify change in the use of targeted strategies following intervention. This will involve counting barrier and facilitator behaviours in 5 min video samples selected from the pre-intervention and post-intervention conversation samples. These counts will be analysed using Poisson trend tests suitable for observations occurring in Poisson distribution. All pre-therapy conversations will be weighted the same as one another, as will all the post-therapy conversations. Outcomes for different participants will be investigated using a test for homogeneity, and where this is significant, the effect for different dyads will be calculated using the Holm–Bonferroni procedure.

Analysis of fidelity and adherence data will inform ongoing training needs. Although fidelity data are sparse for speech and language intervention trials, these processes, deployed in our previous BCPPA study, achieved 87.2% fidelity.^39^ Thus, we have selected 80% as the minimum target for fidelity.

Semi-structured interviews will be recorded and transcribed, and reflexive thematic analysis^61^ will be used to examine acceptability of the intervention across participants living with PPA or other rare dementias. Semi-structured interviews with healthcare professionals and collaborators involved in the recruitment of participants (referral to an SLT) and intervention delivery will be recorded and transcribed. Codebook analysis, informed by implementation frameworks, will be conducted to explore the barriers and facilitators to accessing and delivering the intervention.

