## Methods

### Trial design

This trial was registered retrospectively at ClinicalTrials.gov (ISRCTN16268666). This pilot-feasibility trial employs a randomised controlled design. The protocol follows the Consolidated Standards of Reporting Trials (CONSORT) guidelines, Standard Protocol Items: Recommendations for Interventional Trials (SPIRIT) statement^31^ and the Template for Intervention Description and Replication (TIDieR) checklist and guide.^32^ Comparisons will be made between the treated and the deferred entry groups on pre-treatment versus post-treatment measures. After a 6-week no-treatment phase, deferred participants will then begin intervention. Maintenance will be measured after a 12-week no-treatment period (see figure 1 for an overview of the trial design).

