### Outcome measures

Outcome measures will be collected at four or five time points depending on randomisation. All participants will complete baseline measures on two occasions prior to randomisation to monitor stability. Participants randomised to the immediate intervention condition will complete measures immediately after the intervention and 3 months after receiving the intervention (ie, four times). After completing the two baseline measure sessions, the deferred group will complete the outcome measures again before, immediately after and 3 months after intervention (ie, five times). Table 2 provides an outline for participants’ schedule of involvement including enrolment, intervention and outcome measurement.

**Table 2 T2:** Schedule of enrolment, interventions and outcome measures

Timepoint	Trial period						
	Enrolment			Post-randomisation			Close-out
	*-t_i_* to 0	*t_1_* *Baseline*	*t_2_* *Baseline*	*t_3_* *Post-treatment/ deferral waiting period*	*t_4_** *Deferred entry group post-treatment only*	*t_5_* *12 week post-intervention follow-up*	*t_x_*
Enrolment							
Eligibility screen	X						
Informed consent		X					
Baseline assessments		X	X				
Randomisation			X				
Intervention/comparator							
*BCPPA*							
*Deferred entry group*							
Assessments							
Primary outcome (*CCRSA*)		X	X	X	X*	X	
Primary outcome (*CPIB*)		X	X	X	X*	X	
Secondary outcome (*CAT subtests*)				X	X*		
Secondary outcome (c*onversation samples*)		X	X	X	X*	X	
Secondary outcome (*GAS*)		X	X	X†	X†	X	
Secondary outcome (*personal narrative*)		X	X	X	X*	X	
Secondary outcome (*picture description*)		X	X	X	X*	X	
Secondary outcome (*PACT*)		X	X	X	X*	X	
Secondary outcome (*QCPR*)		X	X	X	X*	X	
Health economics (*EQ5-5D-5L+C*)		X	X	X	X*	X	
Health economics (*ICECAP-O*)		X	X	X	X*	X	
Health economics (*RUD*)		X		X			
Semi-structured interviews			X				X

* Deferred entry group assessment only.

† Completed as part of the intervention in both conditions (ie, immediate treatment and deferred entry group).

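### The between-group model labels time by therapy status rather than by visit; under the protocol's own labels the deferred group's pre/post pair is t3 and t4, which misses the randomised baseline-to-t3 contrast

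*Protocol article*

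**What the plan says.** The Analysis plan section of the protocol article sets the model as a repeated-measures ANOVA with group, immediate or deferred, between subjects and "time (pre-therapy and post-therapy) as a within-subject factor". Its results are to guide the choice of a sensitive outcome measure and the power calculation for the full trial. The Trial design section uses similar labels: "Comparisons will be made between the treated and the deferred entry groups on pre-treatment versus post-treatment measures". Neither sentence names a visit.

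The visits are defined elsewhere. Trial design says: "After a 6-week no-treatment phase, deferred participants will then begin intervention". The Outcome measures section says that, after two baselines, "the deferred group will complete the outcome measures again before, immediately after and 3 months after intervention". In Table 2, t3 is headed "Post-treatment/ deferral waiting period" and t4 is headed "Deferred entry group post-treatment only". The Deferred entry group section presents that group as a control condition equivalent to an NHS waiting list.

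**The concern.** In a deferred-entry trial both groups end up treated, so a time factor defined by therapy status does not mark the same period in the two groups. For the immediate group, before and after therapy are t2 and t3. For the deferred group, the protocol's own words put them at t3 and t4. An analyst who follows the labels would compare two intervals that both contain the intervention. The interaction would then ask whether therapy works differently when delayed, not whether it works.

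The only randomised comparison of treated with untreated dyads is at t3, and the model statement does not point to it. If that contrast were lost, a responsive measure could show no between-group signal. The future sample size might then rest on uncontrolled before-after change in self-rated primary outcomes (CCRSA and CPIB). The Criteria for success section makes both the choice of outcome measure and the sample size estimate conditions for proceeding to a full trial.

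**Working it through.** **Visits side by side** (Outcome measures and Table 2)

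| Visit | Immediate group | Deferred group |
|---|---|---|
| t1, t2 | baseline | baseline |
| t3 | after therapy | end of 6-week wait, before therapy |
| t4 | not assessed | after therapy |
| t5 | 12 weeks after therapy | 12 weeks after therapy |

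No untreated group exists after t3.

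**Inputs.** The Sample size section gives 36 dyads. Randomisation is in blocks of four, stratified by site. A 1:1 ratio is not stated and is assumed here, giving 18 per group. The article gives no alpha, power, effect size or SD for this model, so there is no figure of its own to reproduce. Further assumptions: SD 1, within-person correlation 0.7, two-sided alpha 0.05, effects of 0.5 or 0.8 SD, drift of 0 or -0.02 SD per week, and 6 weeks between successive visits.

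**Formula.** With two groups and two times, the interaction is the difference in mean change: E[change, immediate] - E[change, deferred]. Let dI and dD be the therapy effects in the immediate and deferred groups, and g the drift per week. The immediate group's t2-to-t3 change is dI + 6g.

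- **A. Deferred pair t2, t3 (untreated wait).** The deferred change is 6g, so the interaction is dI.
- **B. Deferred pair t3, t4 (literal labels).** The deferred change is dD + 6g, so the interaction is dI - dD.
- **C. Deferred pair t2, t4.** The deferred change is dD + 12g, so the interaction is dI - dD - 6g.

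**Results** (expected interaction from the formulas; rejection rates simulated, 20,000 runs per setting)

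| Mapping | Effects dI, dD (SD) | Drift per week | Expected interaction (SD) | Rejection rate |
|---|---|---|---|---|
| A | 0.5, 0.5 | 0 | 0.50 | about 47% |
| A | 0.8, 0.8 | 0 | 0.80 | about 85% |
| B | 0.5, 0.5 or 0.8, 0.8 | 0 or -0.02 | 0 | about 5% |
| B | 0.5, 0.3 | 0 | 0.5 - 0.3 = 0.20 | about 12% |
| B | 0.8, 0.5 | 0 | 0.8 - 0.5 = 0.30 | about 20% |
| C | 0.5, 0.5 or 0.8, 0.8 | 0 | 0 | about 5% |
| C | 0.5, 0.5 or 0.8, 0.8 | -0.02 | -6 × (-0.02) = 0.12 | 7% to 8% |

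The simulated mean interactions agree with the formulas to within 0.003 SD. As a check on the power figures under A, the SD of change is √(2 × (1 - 0.7)) = 0.775 and the standard error of the difference is 0.775 × √(2/18) = 0.258. The standardised differences are therefore 0.5/0.258 = 1.94 and 0.8/0.258 = 3.10, consistent with about 47% and 85%. The rejection rates depend on the assumed correlation; the expected interactions do not.

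**The case against.** The strongest reply is that no sentence puts t4 into the model and that the design points the other way. Trial design sets the treated against the deferred group and then says that deferred participants start therapy after the wait. The Deferred entry group section calls that group a control condition. Table 2 gives both groups a shared t3 column, while the immediate group has no t4. A waiting-list trial is ordinarily analysed from baseline to the end of the wait. An article may also leave the mapping of visits to the full protocol or analysis plan, and none of the progression criteria requires a significant interaction.

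Much of this stands. The intended contrast is probably baseline to t3, and the simulation cannot show which visits the team will use. A reader might infer that the trial has discarded its control group, or that the interaction is zero whatever the true effect. The document supports neither. The first needs t4 to be in the model, which is nowhere stated. The second also needs equal effects in both groups and drift that cancels; mappings B and C give 0.20, 0.30 and 0.12 SD when those conditions fail.

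What does not stand is that this is only omitted detail. The article states the factor levels, and they conflict with its own visit labels: to reach the valid contrast one must call the deferred group's t3 post-therapy, although the Outcome measures section places that visit before its therapy. No other sentence overrides the labels. Nor do unequal effects rescue the literal reading, because the interaction then measures only the difference between early and delayed therapy.

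**Conclusion.** The concern holds as a conflict between the stated time levels and the design. Under the protocol's own visit labels, the group-by-time test does not estimate treated versus untreated. Its expectation is about zero if the two groups respond equally and drift cancels; otherwise it reflects the difference in effects and, if t2 is paired with t4, drift as well. With baseline and t3 in both groups, the expected interaction is the immediate group's effect.

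The algebra rests only on the visit schedule and additive effects with constant drift. The power figures are illustrative, since 18 per group, the correlation of 0.7 and the effect sizes are assumptions. The wording should be corrected before analysis, because the results feed the outcome choice and the power calculation.

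**What to change.** In both the Analysis plan and Trial design sections, state that:

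- the randomised between-group comparison uses the pre-randomisation baseline (t2, or the mean of t1 and t2) and t3 in both groups, that is, end of treatment against end of the 6-week wait;
- this contrast supplies the effect estimate for the future power calculation;
- the deferred group's t3-to-t4 change, and the t5 follow-up in both groups, are within-group and descriptive, because no untreated control exists after t3.

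If the full analysis plan already maps the visits this way, the article's wording only needs to be aligned with it. The change needs no new data, visits or measures.

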### Intervention

The BCPPA intervention^29^ was refined to be delivered online via telehealth in four stages over four to six 1-hour sessions for the purposes of this study (BCPPA and other rare dementias). The prior BCPPA intervention was designed to be delivered face to face over four 1-hour sessions for pragmatic reasons.^28^ Given little is known about the optimal dose of BCPPA, the current study aims to explore the dosage implementation by delivering the intervention over 4–6 sessions. Total number of sessions will be jointly decided by the person with PPA, their CP and the treating SLT, based on their progress in the intervention. People with PPA and their CPs will attend all sessions together. Sessions will be facilitated by the RA or local collaborator SLT via Zoom. Video samples will be made by the participants between the two baseline assessments (to ensure naturalness) prior to intervention. From these recordings, the SLT will assess the dyad’s communication and conversation strengths and needs before commencing the programme. A full description of the BC intervention used in this study is provided in the TiDIER documents (online supplemental appendix).

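### The conversation-count analysis is a pre/post Poisson test with no stated group term and no allowance for overdispersion, although the deferred group supplies concurrent control recordings

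*Protocol article*

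**What the plan says.** The Analysis plan (Protocol article) gives two separate procedures.

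- Outcome data in general: "Repeated-measures analyses of variance will be used with group (immediate vs deferred) as a between-subject factor", with time, before and after therapy, as the within-subject factor.
- Conversation data, described afterwards under a procedure of their own: the aim is "to identify change in the use of targeted strategies following intervention". Behaviours are counted in "5 min video samples selected from the pre-intervention and post-intervention conversation samples". Then: "These counts will be analysed using Poisson trend tests suitable for observations occurring in Poisson distribution". On weights: "All pre-therapy conversations will be weighted the same as one another, as will all the post-therapy conversations". Differences between dyads are handled next: "Outcomes for different participants will be investigated using a test for homogeneity, and where this is significant", dyad-level effects follow with Holm-Bonferroni.

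Group does not appear in the conversation procedure, and neither does a dispersion parameter or a dyad effect. Under Trial design, however, the protocol promises in general terms: "Comparisons will be made between the treated and the deferred entry groups on pre-treatment versus post-treatment measures". Table 2 schedules conversation samples at t3, which for the deferred group is the end of the waiting period, and Table 3 says recording is repeated at every later assessment.

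On the baseline recordings, the Intervention section says: "Video samples will be made by the participants between the two baseline assessments (to ensure naturalness) prior to intervention". The therapist assesses the dyad's strengths and needs from these videos.

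**The concern.** Two features of the stated test matter, and they act separately.

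1. **No concurrent control.** Equal weights within each phase reduce the trend test to a two-level before/after score. Any change that would have happened anyway is credited to therapy: disease progression, growing familiarity with the camera, repeated assessment. The randomised comparison that removes such effects is available at t3, but this procedure does not use it.

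2. **Poisson variance.** The test sets the variance equal to the mean. Natural conversations plausibly differ by topic, day and mood, and dyads may differ in how they change. If so, the standard error is too small.

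The Analysis plan uses trial results to pick a suitable and sensitive outcome measure and to size the full trial, and Criteria for success makes finding an appropriate outcome a condition for proceeding. An uncontrolled test with understated variance can flatter this measure relative to those analysed with a group term.

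**Working it through.** **The plan's own figure.** None to reproduce. The protocol gives no alpha, event rate, dispersion or error rate for this analysis.

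**Inputs from the protocol.** 36 dyads (Sample size); blocks of four with balanced groups (Randomisation), taken as 18 v 18; one recorded conversation in the first session plus three home recordings before the second assessment, repeated later (Table 3). The number of 5-minute samples counted per phase is not stated.

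**Assumptions.** Two-sided alpha 0.05; 2 or 4 samples per phase; a mean of 5 to 10 events per sample; conversation-to-conversation coefficient of variation (CV) of 0, 0.3 or 0.5; dyads' underlying rates varying with CV 0.5.

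**Step 1: effect of dispersion.** If the true variance is φ times the mean, the test statistic has standard deviation √φ under the null, so

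true error = 2 × [1 − Φ(1.96/√φ)].

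| φ | 1.96/√φ | true two-sided error | appearing as improvement (half) |
|---|---|---|---|
| 1 | 1.960 | 5.0% | 2.5% |
| 1.5 | 1.600 | 11.0% | 5.5% |
| 2 | 1.386 | 16.6% | 8.3% |
| 3 | 1.132 | 25.8% | 12.9% |
| 4 | 0.980 | 32.7% | 16.4% |

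**Step 2: how much variation gives such a φ.** With mean μ per sample, CV c between conversations and CV d between dyads, the pooled dispersion is φ = 1 + c²μ(1 + d²). With d = 0.5:

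- c = 0.3, μ = 5: 1 + 0.09 × 6.25 = 1.56, error 11.7%
- c = 0.3, μ = 10: 1 + 0.09 × 12.5 = 2.13, error 17.9%
- c = 0.5, μ = 5: 1 + 0.25 × 6.25 = 2.56, error 22.1%
- c = 0.5, μ = 10: 1 + 0.25 × 12.5 = 4.13, error 33.5%

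**Step 3: simulation under no effect.** The pooled test was Z = Σ(post − pre)/√Σ(post + pre) over 36 dyads. False positives were 4–6% for truly Poisson counts, 12–18% at CV 0.3 and 21–33% at CV 0.5, in line with step 2. Half of the inflated rates, about 6–17%, would look like improvement.

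**Step 4: do the later steps protect?** The homogeneity test is a chi-square that itself assumes Poisson variance. With overdispersion and no effect in any dyad, it was significant in 47–100% of simulated trials. Holm-Bonferroni adjusts for the number of tests, not for a wrong variance. If dyad tests are run, at least one dyad was significant after Holm in 19–99.7% of null trials; the top of that range includes extra timepoint variation (CV 0.2).

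**Step 5: the alternative.** A simple comparison of dyad-level log change between arms (18 v 18, same window) had a type I error of 4.0–5.5% across the same scenarios.

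**Step 6: conditional check on target selection.** Suppose each dyad's target is its most frequent barrier (of 3 or 6) and the same baseline samples supply the pre-therapy count. With no true change, the expected post/pre ratio was 0.62–0.98 (mean 3 to 10 events per sample). Neither the selection rule nor the overlap is stated in the protocol. With targets set the same way in both arms, the between-arm comparison kept its error at 3.6–6.5%.

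**The case against.** The strongest reply has four parts.

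- **The promise under Trial design may cover these counts, and a fuller analysis plan may exist.** The procedure follows an earlier study that is not shown. This stands as far as it goes: one can say only that no group term is stated. But the ANOVA paragraph names group explicitly and the conversation procedure names a specific test without it, so the text as fixed does not deliver the promised comparison.
- **A within-dyad contrast answers a stated question.** Feasibility asks whether measures are sensitive to change before, after and three months after therapy. That is a reason to keep the contrast as a description. It does not make it evidence of a treatment effect, nor does it justify Poisson standard errors.
- **Every dispersion input is assumed.** True. The direction is certain if counts are overdispersed; the size is not.
- **This is a secondary outcome in a pilot,** and no progression criterion requires a significant Poisson test. True, and it limits the severity.

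Three stronger readings are tempting and are not supported. A reader might infer that the deferred group's t3 recordings will be counted as extra pre-therapy data; the protocol does not say which timepoints supply the samples. A reader might infer that data will always be pooled; pooling gives way to dyad-level results if homogeneity is rejected. A reader might infer a built-in bias towards improvement because targets are chosen from the counted baseline videos. Which clips are counted is not stated, the first-session conversation is a separate recording, dyads choose behaviours they wish to change rather than the most frequent ones, and for facilitators the direction of any regression to the mean is not established. Masking raters to timepoint would not remove such a bias, but its presence is conditional.

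**Conclusion.** The point holds in limited form. The stated analysis of the conversation counts is a before/after Poisson test with no group term and no dispersion allowance, in a randomised trial that collects the control recordings needed to do better. As written it cannot isolate treatment from time. Its nominal 5% error becomes about 17% at dispersion 2 and 26% at dispersion 3, both assumed, with about half of the errors in the direction of improvement. That is material inflation, but it does not show that a false improvement is likely. A false improvement becomes likely mainly if targets are selected on the same recordings that are counted, which the protocol leaves open. The homogeneity and dyad-level steps are no safeguard. The consequence is a risk of overrating this measure's sensitivity when planning the full trial. This should be fixed; it does not threaten the pilot as a whole.

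**What to change.** 1. Make the main analysis of these counts a between-arm comparison (immediate versus deferred) of change from baseline to t3. Use a dyad-clustered negative binomial or quasi-Poisson model adjusted for site, or a simple between-arm comparison of dyad-level log change. State how the comparison promised under Trial design applies to these counts.
2. Keep the within-dyad pre/post contrast, including the deferred group's later treatment period, as descriptive, with overdispersion-robust errors. Replace the Poisson-based homogeneity and dyad tests, or label them exploratory.
3. State which recordings supply the counted samples at each timepoint. Log which clips were used for goal setting and, where possible, take the counted baseline samples from other recordings.
4. Report total barrier and facilitator counts alongside the targeted ones. Totals are defined alike in both arms. Outcome measures places goal setting within the intervention, so deferred dyads may have no targets at t3; compare targeted counts between arms only if targets are defined the same way in both.

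Cost: a change of analysis wording, a short log and slightly more analysis work. Intervals will be wider. No extra recordings or participants are needed.
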